### **11.7.2 Dose modification for FOLFOX, CapeOX, and 5-FU and Capecitabine during radiation**

FOLFOX, CapeOX, and 5-FU and capecitabine during radiation are standard regimens that have been widely used for the treatment of colon and rectal cancer for more than a decade. Investigators should refer to package and inserts and local pharmacy practices for a

complete list of potential toxicities, and adhere to best practices. If chemotherapy is held during radiation, radiation may be continued at physician discretion.

Treatment interruptions and modifications should be made at the discretion of the treating physician. The following dose reduction and modification tables should be used as a guide. If the treating physician feels that it is feasible to continue treatment without interruption, and/or use a modification other than what is indicated below, and without putting the patient at undue risk, then the treating physician may proceed with treatment as planned.

Dose Levels of sensitizing chemotherapy during radiation are as follows:

| Dose Level | 5-FU Infusion | Capecitabine    |
|-------------------------------|----------------------------------|------------------------|
| 0                             | 225 mg/m  /day       | 1650 mg/m  |
| -1                            | 175 mg/m  /day       | 1237 mg/m  |
| -2                            | 135 mg/m  /day       | 825 mg/m   |
| -3                            | 100 mg/m  /day       | 650 mg/m   |

1 Dose level 0 refers to the starting dose

2 There no dose level restrictions for either infusional 5-FU or capecitabine during chemoradiation. Patients will remain active in the study and on schedule irrespective of any dose modifications to 5-FU and capecitabine made by the treating physician.

Dose reductions for Oxaliplatin, Leucovorin, and 5-FU are as follows:

| Drug   | Dose Level 0
(mg/m^2) | Dose Level -1
(mg/m^2) | Dose Level -2
(mg/m^2) | Dose Level -3
(mg/m^2) |
|---------------|--------------------------------------------|---------------------------------------------|---------------------------------------------|---------------------------------------------|
| Oxaliplatin   | 85                                         | 65                                          | 50                                          | 0                                           |
| Leucovorin    | 400                                        | 320                                         | 260                                         | 260                                         |
| 5-FU bolus    | 400                                        | 320                                         | 260                                         | 260                                         |
| 5-FU Infusion | 1200                                       | 900                                         | 720                                         | 720                                         |

The following tables describe those modifications to be used for Day 1 of a new cycle of FOLFOX therapy and are suggested guidelines for treatment modifications. All dose modifications in a new cycle are based upon the most severe toxicity observed in the previous cycle. Any modifications to treatment should be made at the discretion of the treating physician.

| Dose Modification for Oxaliplatin, 5-FU, and Leucovorin               |                                                                                     |                                                                            |                                                                            |
|------------------------------------------------------------------------------|-------------------------------------------------------------------------------------|----------------------------------------------------------------------------|----------------------------------------------------------------------------|
| Toxicity: CTCAE grade                                                 | Oxaliplatin                                                                  | 5-FU                                                                | LV                                                                  |
| Neutropenia or thrombocytopenia                                       |                                                                                     |                                                                            |                                                                            |
| Grade 2                                                                      | Hold to resolution to $\leq$ grade 1. Resume at same dose.                          | Hold to resolution to $\leq$ grade 1. Resume at same dose.                 | Hold to resolution $\leq$ grade 1. Resume at same dose.                    |
| Grade 3 or 4                                                                 | Hold to resolution to $\leq$ grade 1. Resume at dose decreased by 1 level.          | Hold to resolution to $\leq$ grade 1. Resume at dose decreased by 1 level. | Hold to resolution to $\leq$ grade 1. Resume at same dose.                 |
| Neutropenic fever or infection                                        | Hold to resolution to $\leq$ grade 1. Resume at dose decreased by 1 level.          | Hold to resolution to $\leq$ grade 1. Resume at dose decreased by 1 level. | Hold to resolution $\leq$ grade 1. Resume at same dose.                    |
| Diarrhea                                                              |                                                                                     |                                                                            |                                                                            |
| Grade 3 or 4                                                                 | Hold to resolution to $\leq$ grade 2. Resume at dose decreased by 1 level.          | Hold to resolution to $\leq$ grade 2. Resume at dose decreased by 1 level. | Hold to resolution to $\leq$ grade 2. Resume at same dose.                 |
| Mucositis                                                             |                                                                                     |                                                                            |                                                                            |
| Grade 2                                                                      | No modification                                                                     | No modification                                                            | No modification                                                            |
| Grade 3                                                                      | No modification                                                                     | Hold to resolution to $\leq$ grade 2. Resume at dose decreased by 1 level. | Hold to resolution to $\leq$ grade 2. Resume at dose decreased by 1 level. |
| Grade 4                                                                      | Hold to resolution to $\leq$ grade 2. Resume at dose decreased by 1 level.          | Hold to resolution to $\leq$ grade 2. Resume at dose decreased by 1 level. | Hold to resolution to $\leq$ grade 2. Resume at dose decreased by 1 level. |
| Vomiting                                                              |                                                                                     |                                                                            |                                                                            |
| Grade 0-2                                                                    | No modification                                                                     | No modification                                                            | No modification                                                            |
| Grade 3                                                                      | Hold to resolution to $\leq$ grade 2. Resume at dose decreased by 1 level.          | Hold to resolution to $\leq$ grade 2. Resume at same dose.                 | Hold to resolution to $\leq$ grade 2. Resume at same dose.                 |
| Grade 4                                                                      | Hold to resolution to $\leq$ grade 2. Resume at dose decreased by 1 level.          | Hold to resolution to $\leq$ grade 2. Resume at dose decreased by 1 level. | Hold to resolution to $\leq$ grade 2. Resume at same dose.                 |
| Pulmonary                                                             |                                                                                     |                                                                            |                                                                            |
| Cough, dyspnea, hypoxia, pneumonitis or pulmonary infiltrates $\geq$ grade 3 | Hold oxaliplatin until interstitial lung disease is ruled out. Resume at same dose. | No modification                                                            | No modification                                                            |
| Other non-hematologic toxicities                                      |                                                                                     |                                                                            |                                                                            |
| Grade 0-2                                                                    | No modification                                                                     | No modification                                                            | No modification                                                            |

|              |                                                                            |                                                                            |                                                            |
|--------------|----------------------------------------------------------------------------|----------------------------------------------------------------------------|------------------------------------------------------------|
| Grade 3 or 4 | Hold to resolution to $\leq$ grade 2. Resume at dose decreased by 1 level. | Hold to resolution to $\leq$ grade 2. Resume at dose decreased by 1 level. | Hold to resolution to $\leq$ grade 2. Resume at same dose. |
|--------------|----------------------------------------------------------------------------|----------------------------------------------------------------------------|------------------------------------------------------------|

Dose reductions for Oxaliplatin and Capecitabine are as follows:

| Drug         | Dose Level 0 
(mg/m  ) | Dose Level -1
(mg/m  ) | Dose Level -2
(mg/m  ) | Dose Level -3
(mg/m  ) |
|--------------|---------------------------------------------------|---------------------------------------|---------------------------------------|---------------------------------------|
| Oxaliplatin  | 130                                               | 100                                   | 80                                    | 65                                    |
| Capecitabine | 1000                                              | 800                                   | 640                                   | 510                                   |

 Dose Level 0 refers to the starting dose.

The above table describes those modifications to be used for Day 1 of a new cycle of CapeOx therapy and are suggested guidelines for treatment modifications. All dose modifications in a new cycle are based upon the most severe toxicity observed in the previous cycle. Any modifications to treatment should be made at the discretion of the treating physician.

#### 11.7.2.1 Retreatment Criteria for 5-fluorouracil, Leucovorin, and Oxaliplatin

Subsequent to dose delays, patients may be re-treated with chemotherapy provided that all grade 3-4 toxicities have resolved to < grade 1.

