In addition, we will calculate therapy compliance using the following measures: the number of days RT was held, the number of RT delays of  $\geq 1$  week, the number of dose delays and the number of dose reductions in INCT and CNCT. We will also calculate the rate of select hematologic events (as outlined in 17.2), select non-hematologic events (as outlined in 16.0), and unexpected Grade 3 or higher non-hematologic adverse events and surgical complications in each treatment arm. Comparisons will be done using the Wilcoxon Rank Sum test or the Fisher’s Exact test.

**14.3 Secondary objective 2.:** *To measure patient-reported functional outcomes and QoL in patients with LARC treated with NCT, CRT and NOM, and compare these to patients treated with TME.*

The primary analyses for this aim will use data combined across both treatment arms; however, differences according to treatment will also be investigated. The primary endpoint will be QoL as measured one year from the end of TNT. Secondary endpoints will be bowel, sexual, and bladder function. While the subscales will be reported, the primary secondary endpoints will be the total scores on the BFI, FSFI and IIEF. With a total of 325 patients accrued, we expect that 129 patients will obtain complete clinical response and 196 will undergo TME. Approximately 15 to 30 patients initially treated with NOM are expected to cross over to TME at some point during follow-up. For the primary analyses, the NOM group will include these cross-overs on an intent-to-treat analysis. In secondary analysis, patients who eventually crossed over to receive surgery will be included in the TME group. We define this analysis as a comparison between TME vs. durable NOM. Durable NOM is defined as 3-year disease-free survival. We expect that 70% of patients will complete the QoL assessment at 1 year. This response rate takes into account refusals to complete the QoL

questionnaires, and the approximately 20% of patients who will develop distant disease or die before the 1-year time point. Thus, at 1 year we expect to have information on 94 TME patients and 62 NOM patients.

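### The FOLFOX re-treatment condition in Section 11.7.2.1 conflicts with the dose-modification table's restart threshold for most grade 3-4 non-hematologic toxicities, and no precedence is stated

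*Protocol*

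**What the plan says.** Section 11.7.2.1 covers 5-fluorouracil, leucovorin and oxaliplatin. After a dose delay, re-treatment is allowed on condition that "all grade 3-4 toxicities have resolved to < grade 1". The sentence is worded as a condition, applies one bound to every grade 3-4 toxicity, and does not refer to the tables.

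The FOLFOX table in Section 11.7.2 covers the same three drugs and sets "modifications to be used for Day 1 of a new cycle of FOLFOX therapy and are suggested guidelines for treatment modifications". Its restart instruction depends on the toxicity:

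- For grade 3 or 4 neutropenia or thrombocytopenia, and for neutropenic fever or infection, oxaliplatin and 5-FU carry "Hold to resolution to $\leq$ grade 1. Resume at dose decreased by 1 level". Leucovorin has the same grade bound.
- For grade 3 or 4 diarrhea, oxaliplatin and 5-FU carry "Hold to resolution to $\leq$ grade 2. Resume at dose decreased by 1 level".
- Elsewhere among the non-hematologic rows, for example 5-FU and leucovorin after grade 3 vomiting, the entry is "Hold to resolution to $\leq$ grade 2. Resume at same dose".

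Section 11.7.2 also says of its tables: "The following dose reduction and modification tables should be used as a guide". It leaves interruptions and modifications to the treating physician.

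Section 14.2 lists, among the compliance measures to be compared between arms, "the number of dose delays and the number of dose reductions in INCT and CNCT". The same section calls the compliance and adverse-event objectives exploratory.

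**The concern.** Two passages a page or so apart give different recovery grades for restarting the same drugs after the same severe toxicity. A patient held for grade 3 diarrhea who has improved to grade 2 may restart under the table but not under Section 11.7.2.1. No sentence says which passage governs, so two sites in this multicenter trial could both follow the protocol and act differently. An auditor checking compliance under Section 16.1.1 has no stated rule for which threshold to apply.

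The statistical stake is smaller. Dose delays are a planned compliance measure, and what a site does at the restart decision can feed into that count.

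**Working it through.** No sample size, power or error rate depends on this point, so the check is a comparison of thresholds and a count of cells.

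**Inputs.** The bound in Section 11.7.2.1, and every row of the FOLFOX table in Section 11.7.2 labelled grade 3, grade 4, grade 3 or 4, or at least grade 3. There are 8 such rows and 3 drugs, so 8 × 3 = 24 cells. The neutropenic fever or infection row carries no grade label and is counted separately.

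| Table row | Cells restarting at ≤ grade 1 | Cells restarting at ≤ grade 2 | Cells with no restart grade |
|---|---|---|---|
| Neutropenia or thrombocytopenia, grade 3 or 4 | 3 | 0 | 0 |
| Diarrhea, grade 3 or 4 | 0 | 3 | 0 |
| Mucositis, grade 3 | 0 | 2 | 1 (oxaliplatin, not modified) |
| Mucositis, grade 4 | 0 | 3 | 0 |
| Vomiting, grade 3 | 0 | 3 | 0 |
| Vomiting, grade 4 | 0 | 3 | 0 |
| Pulmonary, grade 3 or higher | 0 | 0 | 3 |
| Other non-hematologic, grade 3 or 4 | 0 | 3 | 0 |
| **Total** | **3** | **17** | **4** |

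Check: 3 + 17 + 4 = 24. The neutropenic fever or infection row adds 3 cells at ≤ grade 1. Cells that state a restart grade are therefore 3 + 17 + 3 = 23, and none of them uses a bound below grade 1.

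**Two readings of the sign in Section 11.7.2.1.** The table's signs survive in the text as less-than-or-equal, whereas Section 11.7.2.1 shows a bare less-than. Whether the sign was printed that way or lost its lower bar when the PDF was read cannot be settled from the text, so both readings are shown.

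| Reading | Highest grade allowed by 11.7.2.1 | Gap to the ≤ grade 1 cells (3 + 3 = 6) | Gap to the ≤ grade 2 cells (17) |
|---|---|---|---|
| Strict (below grade 1) | 0 | 1 − 0 = 1 grade | 2 − 0 = 2 grades |
| Less than or equal to grade 1 | 1 | 1 − 1 = 0, they agree | 2 − 1 = 1 grade |

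The conflict in the 17 non-hematologic cells stands under either reading. The conflict in the 6 hematologic cells stands only under the strict one.

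**Effect on the dose-delay measure.** Section 14.2 counts delays of chemotherapy, not their length. A stricter restart bound mainly lengthens a hold that is already counted once. The count itself changes only if a patient at grade 1 or 2 on a planned Day 1 is treated under one passage and held under the other, or if a longer hold displaces a later cycle. Estimating how often this happens would need rates of toxicity resolution by cycle. The documents give none, so no figure is offered.

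**The case against.** The strongest reply is discretion. Section 11.7.2.1 sits inside Section 11.7.2, which leaves interruptions and modifications to the treating physician and lets that physician depart from the tables where this brings no undue risk. On this view neither passage binds, and even a reconciled threshold would not standardize hold lengths. The second part stands: the fix will not make delays uniform. The first does not remove the problem, because permission to depart from a rule does not say what the rule is.

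It can also be said that a patient who meets the stricter bound meets both, so the stricter bound governs by default. The protocol does not say this, and the table's restart grades would then have no function.

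The limits on the effect stand as well. The compliance objective is exploratory. Both arms follow the same text, and randomization is stratified by institution (Section 15.2), so differences in site interpretation should be roughly balanced between arms.

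Four stronger readings are tempting and are not supported:

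- That every grade 3-4 toxicity is affected. The pulmonary row, and oxaliplatin in grade 3 mucositis, state no restart grade.
- That the 44% grade 3-4 neutropenia in Section 11.1 measures the problem. It is an incidence of toxicity, it says nothing about recovery by a planned Day 1, and it concerns a row where the conflict depends on the sign.
- That the comparison between arms is biased. No direction is shown.
- That harm to patients can be inferred. The documents show two incompatible instructions, not a consequence.

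**Conclusion.** The protocol contradicts itself on when FOLFOX may restart after grade 3-4 diarrhea, mucositis, vomiting and other non-hematologic toxicity. This covers 17 of the 24 cells in the grade 3-4 rows. The gap is two grades if the sign in Section 11.7.2.1 is strict and one grade if less-than-or-equal was meant. The grade 3-4 blood-count row and the neutropenic fever or infection row conflict by one grade on the strict reading only.

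The consequence is two incompatible written restart conditions with no precedence, and possibly some added noise in an exploratory count of dose delays. The size of that noise cannot be computed from the documents. The design figures and analysis for 3-year disease-free survival do not depend on this point.

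The conclusion rests on the two passages applying to the same drugs, which their titles and headings show, and on the absence of any rule of precedence in Section 11.7.2 or 11.7.2.1. No view is taken on which threshold is right.

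**What to change.** Amend Section 11.7.2.1 and the FOLFOX table so that one recovery threshold applies to each toxicity, and state which passage governs if they differ. Confirm in the same amendment whether the sign in Section 11.7.2.1 is strict. The thresholds are for the sponsor to choose.

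The cost is a wording amendment, with no change to sample size or the primary analysis. It cannot alter holds that have already happened, and Section 14.1 reports that the originally planned accrual is complete. For patients already treated, report dose delays as observed and note beside the result that the two passages differed.

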#### 11.7.2.2 Dose modifications of Leucovorin

There are no dose modifications for Leucovorin. If the 5-FU is skipped (bolus and infusion), then Leucovorin should also be held. If Leucovorin is not available, it is at the discretion of the treating physician to administer FOLFOX without Leucovorin or to use Fusilev (Levoleucovorin) as an alternative to Leucovorin. If Fusilev (Levoleucovorin) is used as a substitute for Leucovorin, the patient should receive a dose of 50% of the protocol-specific dose of racemic Leucovorin. In keeping with the protocol-specific Leucovorin dose of 400 mg/m^2, the Fusilev equivalent is 200 mg/m^2.

#### 11.7.3 Dose modification for Hand-Foot Syndrome (HFS)

The Common Terminology Criteria for Adverse Events (CTCAE) version 4.0 will be used. Grade 1 HFS is defined as numbness, dysesthesia/paresthesia, tingling, painless swelling or erythema of the hands and/or feet, and/or discomfort which does not disrupt normal activities of daily living. Grade 2 HFS is defined as painful erythema and swelling of the hands and/or feet and/or discomfort affecting the patient's normal activities of daily living. Grade 3 HFS is defined as moist desquamation, ulceration, blistering and severe pain of the hands and/or feet and/or discomfort that causes the patient to be unable to work or perform normal activities of daily living. If Grade 2 or 3 HFS occurs, administration of capecitabine should be interrupted until the event resolves or decreases to Grade 1. Subsequent doses of capecitabine should be decreased.

